### Statistical analysis plan

The data will be analysed on intention to treat (ITT) and follow Consolidated Standards of Reporting Trials reporting guidelines (http://www.consort-statement.org/). Randomised participants who are not found to have lung cancer will be included in the primary analysis, but a modified ITT analysis excluding these participants will also be performed. Analyses will be adjusted for centre and for design factors included in the cohort minimisation (eg, the operating surgeon). As the allocation to VATS or open lobectomy is minimised by surgeon, clustering may occur within the dataset. The structure of the data, that is, nesting of patients by surgeon and centre, will be accounted for in the primary analysis.

Patient-reported outcome scores (HRQoL) and will be compared using a mixed regression model, adjusted for baseline measures where appropriate. Changes in treatment effect with time will be assessed by adding a treatment × time interaction to the model and comparing models using a likelihood ratio test. Deaths will be accounted for by modelling HRQoL and survival jointly. Model fit will be assessed and alternative models and/or transformations (eg, to induce normality) will be explored where appropriate.

Missing items or errors on questionnaire measures will be dealt with according to the scoring manuals or via imputation methods. For other outcomes a complete case analysis will be undertaken if fewer than 5% of cases have missing data, otherwise multiple imputation methods will be considered. Compliance rates will be reported, including the numbers of patients who have withdrawn from the study, have been lost to follow-up or died. Causes of death for trial participants will be recorded.

Frequencies of adverse events will be described. Treatment differences will be reported with 95% CIs. In this study of 498 patients, we are underpowered to detect differences in survival of less than approximately 20% at 2 years. However, survival rates and 95% CIs will be reported.

One subgroup analysis is planned, comparing pain scores by type of analgesia (paravertebral block vs intercostal block). This will be tested by adding an analgesia by treatment interaction term to the model. In addition, as an exploratory analysis we will report pain scores within the VATS lobectomy group by number of port sites (single vs multiple port sites), but a formal comparison between the sub-sets of the VATS group is not planned.

The primary analysis will take place when follow-up is complete for all recruited participants. Interim analysis will be decided in discussion with the Data Monitoring and Safety Committee. There is no intention to compare any outcomes between groups after phase 1; the only analyses will be descriptive statistics to summarise recruitment to decide whether the trial satisfies the progression criteria.

*Economic Evaluation:* For the economic evaluation, unit costs will be derived from nationally published sources and attached to resource use data, and the total costs per participant calculated. Responses to the EQ-5D-5L will be assigned valuations derived from published UK population tariffs,^38–40^ and combined with survival to calculate QALYs gained per participant. Missing resource use and EQ-5D-5L data will be handled using multiple imputation methods.^41^ From the average costs and QALYs gained in each trial group, the incremental cost-effectiveness ratio will be derived, producing an incremental cost per QALY gained of VATS lobectomy compared with open lobectomy. Univariate and multivariate sensitivity analyses will assess the impact of varying key parameters in the analysis on baseline cost-effectiveness results. Results will be expressed in terms of a cost-effectiveness acceptability curve, which indicates the likelihood that VATS lobectomy is cost-effective for different levels of willingness to pay for health gain.

*Qualitative analysis*: Analysis of qualitative data will involve transcribing the audio-recorded consultations, interviews and meetings with consent. The QRI researcher will (a) analyse the transcripts and notes thematically using techniques of constant comparison^42^ and case study approaches to explore the ‘clear obstacles’ and ‘hidden challenges^30^ to recruitment in VIOLET, and (b) employ targeted conversation analysis^27^ to focus on areas in the consultations where communication appears to struggle or break down to identify aspects of recruitment that could be improved. Subsets of interview and consultation transcripts will be independently coded by two qualitative researchers, with the coding discussed and any discrepancies resolved, to establish a coding frame that can be applied to other transcripts. Descriptive accounts will summarise key challenges to recruitment. Anonymised findings will be documented and synthesised for presentation to the RCT CI.

*Access to study data:* Access to the study data will be limited to authorised personnel. Data will be collected and retained in accordance with the UK Data Protection Act 1998. An anonymised dataset will be held for future research as per the National Institute for Health Research contractual arrangements.

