### Study population

Participating *centres* will only be eligible if they meet all the following eligibility criteria: (1) NHS Trust with an established and accredited lung cancer multi-disciplinary team (MDT). (2) Centre carries out ≥40 VATS lobectomies each year and employs at least one surgeon who has carried out ≥50 VATS lobectomies.

Participating *surgeons* will be eligible for the trial if they have performed ≥50 VATS lobectomies. Prospective surgeons will be required to submit their activity logs, which will be validated against local audit data from the MDT meetings, prior to acceptance to the trial. Lobectomy via open surgery is currently standard procedure and therefore surgical ability and competence will be assured by specialist UK General Medical Council (GMC) registration.

*Patients* may enter the study if all the following apply:

Adult aged ≥16 years of age.Able to give written informed consent, undergoing either: (a) lobectomy or bilobectomy for treatment of known or suspected primary lung cancer beyond lobar orifice* in tumour, node, metastases TNM8 stage cT1-3 (by size criteria, equivalent to TNM7 stage cT1a-2b) or cT3 (by virtue of 2 nodules in the same lobe), N0-1 and M0 or (b) undergoing frozen section biopsy with the intention to proceed with lobectomy or bilobectomy if primary lung cancer with a peripheral tumour beyond a lobar orifice* in TNM8 stage cT1-3 (by size criteria, equivalent to TNM7 stage cT1a-2b) or cT3 (by virtue of 2 nodules in the same lobe), N0-1 and M0 is confirmed.Disease suitable for both minimal access (VATS lobectomy) and lobectomy via open surgery.

*In the case of bilobectomy, the distance for the ‘lobar’ orifice is in reference to the bronchus intermedius.

*Patients* may not enter the study if any of the following apply:

Previous malignancy that influences life expectancy.Pneumonectomy, segmentectomy or non-anatomic resection (eg, wedge resection) is planned.Patient has a serious concomitant disorder that would compromise patient safety during surgery.Planned robotic surgery.

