### Randomisation

Participants will be randomised in a 1:1 ratio to either VATS lobectomy or open lobectomy. Randomisation will take place through a secure internet-based randomisation system, access to which will be restricted to authorised study personnel. Cohort minimisation (with a random element incorporated) will be used to ensure balance across groups with respect to the surgeon and the allocation will be stratified by centre.

Due to the pragmatic nature of this trial there will inevitably be some variability between surgeons, the surgical teams and the perioperative processes. Such heterogeneity is important as this accurately reflects real clinical practice.

Randomisation will be performed 1 week prior to the planned operation date, once eligibility has been confirmed and written consent taken by a research nurse. This will allow sufficient time for operating theatre schedules to be arranged. If there is a change in surgeon after randomisation, the analysis will account for the surgeon responsible for performing the operation and not the surgeon originally allocated to the patient.

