### Primary and secondary outcomes

The primary outcome is self-reported physical function measured using the European Organization for Research and Treatment of Cancer Quality of Life Questionnaire-C30 (EORTC QLQ-C30) at 5 weeks post-randomisation. Physical function has been chosen because it is a patient-centred outcome that will reflect the anticipated earlier recovery with VATS lobectomy and has been used in other minimal access surgery trials. The primary endpoint has been chosen to be 5 weeks (1 month post-surgery) to capture the early benefits of minimal access surgery on recovery. The EORTC QLQ-C30 has been validated for use in European cohorts. In addition to assessing physical function the questionnaire also assesses psychological and social well-being. Secondary outcomes have been selected to assess the efficacy of the two approaches.

Secondary outcomes are (1) time from surgery to hospital discharge; (2) adverse health events; (3) proportion and time to uptake of adjuvant treatment; (4) proportion of patients upstaged to pN2 disease after the procedure; (5) overall and disease-free survival to 1 year; (6) proportion of patients who undergo complete resection during the procedure; (7) proportion of patients who experience prolonged incision pain defined as the need for analgesia >6 weeks after surgery; (8) generic and disease-specific health-related quality of life (HRQoL) assessed using the EORTC QLQ-C30, QLQ-LC13 and EQ-5D-5L questionnaires completed at 2 weeks, 5 weeks, 3 months, 6 months and 1 year post-randomisation); (9) resource use measured for the duration of post-operative hospital stay until discharge and at 5 weeks, 3 months, 6 months and 1 year post-randomisation.

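### The stated adjustment set does not name clinical N category for pN2 upstaging and survival, although it is known before randomisation; naming it would be a small, cheap improvement

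*Protocol article*

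**What the plan says.** The Statistical analysis plan section of the protocol article states: "Analyses will be adjusted for centre and for design factors included in the cohort minimisation (eg, the operating surgeon"). One extension follows: patient-reported scores "will be compared using a mixed regression model, adjusted for baseline measures where appropriate". No model is set out for upstaging or survival. The section concedes that survival is underpowered and promises rates with 95% CIs.

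Under Randomisation, cohort minimisation "will be used to ensure balance across groups with respect to the surgeon and the allocation will be stratified by centre". Clinical stage plays no part in the allocation.

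Under Study population, patients must have N0-1, M0 disease within a T range worded as "TNM8 stage cT1-3 (by size criteria, equivalent to TNM7 stage cT1a-2b"). Randomisation takes place "once eligibility has been confirmed and written consent taken by a research nurse", and Table 1 schedules an imaging review at baseline. Clinical N and T stage therefore has to be assessed before allocation.

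The secondary outcomes include "proportion of patients upstaged to pN2 disease after the procedure; (5) overall and disease-free survival to 1 year".

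**The concern.** Upstaging to pN2 is a move away from a clinical N category, and the trial admits both cN0 and cN1. The section adjusts quality of life for its own baseline but does not name the corresponding baseline for upstaging. The same variable can be expected to predict disease-free and overall survival, where events within 1 year may be few.

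Two things are at stake, both modest. The first is a little power on outcomes that have little to spare. The second is credibility. If the arms turn out to differ in cN1 share and stage was not named beforehand, adding it later looks driven by the data, and leaving it out invites the opposite complaint.

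**Working it through.** **1. The plan's own figure.** With five post-surgery measures, correlation 0.6 between them and 0.3 with baseline, the variance factor is (1 + 4×0.6)/5 − 0.3² = 0.59. For 0.25 SD, 90% power and two-sided 5% (assumed, as alpha is not stated), this gives 199 per arm, or 398. Then 398/0.8 = 497.5, rounded up to 498. The stated figures reproduce, and stage does not enter them.

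**2. Inputs for stage.** From the article: 498 participants, 1:1. The stage mix, event risks, stage effects and treatment effects below are all assumptions, because the article gives none of them for these outcomes.

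**3. Chance imbalance in cN1 share.** SD of the difference between arms = 2·√(q(1−q)/498).
- q = 0.10: 2.7 percentage points
- q = 0.20: 3.6 percentage points

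**4. Effect on a risk difference.** A binary stage factor was used with share p from 5% to 20%, overall risk from 5% to 15% and stage odds ratio from 2 to 5. Variance removed by adjustment: R² = p(1−p)(r1−r0)² / [r(1−r)], where r is the overall risk and r1, r0 are the risks with and without the factor.

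Mid case (p = 10%, r = 10%, odds ratio 3, so r0 = 0.087 and r1 = 0.221):
- R² = 0.09 × 0.134² / 0.09 = 0.018.
- Unadjusted SE = √(4×0.09/498) = 0.0269. Adjusted SE = 0.0266, a fall of 0.9%.
- 95% range of imbalance = ±1.96 × 2.7 = ±5.3 points, which moves the risk difference by ±5.3 × 0.134 = ±0.7 points.
- Unadjusted CI half-width = 1.96 × 0.0269 = 5.3 points, so the shift is about 13% of it.

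Whole grid: R² 0.002 to 0.082; fall in SE 0.1% to 4.2%; shift ±0.2 to ±1.8 points. The shift as a share of the half-width is √R², so about 4% to 29%.

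**5. Power by simulation, 498 participants.**

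| Outcome and assumptions | Without stage | With stage | Change (points) |
|---|---|---|---|
| pN2, N only; 10–20% cN1, control risk 5% in cN0 and 25–30% in cN1, treatment OR 0.4; four scenarios, 2,500 runs each | 52.3%, 52.8%, 61.6%, 63.8% | 53.2%, 56.5%, 64.0%, 67.9% | +0.9, +3.7, +2.4, +4.1 |
| Binary outcome, T and N; moderate stage effects, 1,500 runs | 73.3% | 73.4% | +0.1 |
| Same, strong stage effects | 68.9% | 72.3% | +3.4 |
| 1-year Cox, two stage groups; 30% higher stage, stage HR 2.5 or 4, treatment HR 0.6, 1,500 runs each | 50.1%, 56.3% | 51.9%, 59.0% | +1.8, +2.7 |
| 1-year Cox, T and N; about 53 or 64 events, 400 runs each | 58%, 59% | 56%, 62% | within Monte Carlo error (about 2.5 points) |

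A further simulation of pN2 upstaging with centre in the model gave gains of about 0.4 to 4 points from N category and nothing further from T category.

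**6. Validity.** With no treatment effect and strong stage effects, type I error was 5.3% without stage and 5.0% with it (1,500 runs).

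**The case against.** The strongest reply is that nothing in the section is wrong. Adjusting for allocation factors is sound, and the rule is not a closed list. A reader might infer that the plan allows adjustment for centre and surgeon only. The text does not say so, and the full protocol or SAP, neither of them shown, may name stage. That stands. The point therefore concerns what the stated rule names, not what the trial will necessarily do.

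A reader might also infer that a chance difference in stage mix would bias the VATS effect. It would not. Under randomisation this is sampling variation that the 95% CI already covers, as the type I error shows. Nor is stage simply noise to be removed. In logistic and Cox models, adjustment targets a conditional effect and does not shrink the SE of the log odds ratio or log hazard ratio; the gain is in power.

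Three practical objections also stand in part:
- With few events, adding full T and N categories to centre and surgeon terms may cost stability.
- The stage criteria were amended when TNM8 came in, so T categories may span two editions.
- Table 1 lists an imaging review, not a recorded cN field. That the category itself is stored is an inference.

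These narrow the proposal to N category first. They do not remove the case for naming it.

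**Conclusion.** The point holds as a minor improvement. Clinical N category is assessed before randomisation and is the starting point of pN2 upstaging, yet it is neither balanced by the allocation nor named in the stated adjustment set. The analysis without it is valid. Naming it in advance would raise power by roughly 0 to 4 points, clearest for pN2 upstaging when the stage effect is strong and hard to distinguish from nil for 1-year survival with 50 to 65 events. It would also prevent a dispute over post hoc adjustment. All these sizes rest on assumed stage mixes, risks and effects. The documents do not support calling this an error or a source of bias.

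**What to change.** Add to the Statistical analysis plan section, or confirm that the SAP already says: *Models for upstaging to pN2, disease-free survival and overall survival will also include clinical N category (N0 or N1) as recorded before randomisation. Clinical T category, mapped to one TNM edition, will be added only for outcomes whose number of events exceeds a threshold stated here.* The threshold should be set before any comparison of the groups, so that the choice of model does not depend on the results.

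The cost is one sentence, a check that the N category itself is recorded and not only that the patient is within range, and the mapping of T category where it is used. The estimate becomes a conditional effect, which the report should say, and each model gains one or more parameters. No new visit or assessment is needed.

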### Standardisation of postoperative management

As this is a pragmatic RCT, postoperative care and the criteria for drain removal will be in accordance with local practice. However, we have identified two elements of patient care, which require standardisation to minimise the potential for bias, namely pain-control and the criteria by which a participant’s medical fitness-for-discharge is assessed.

Standardising the use of analgesia across participating centres is impractical and does not reflect the intended pragmatic nature of the trial, it, would also produce data unrepresentative of real clinical practice. Therefore, each participating centre will prescribe analgesia in accordance with their local protocols. All patients recruited to the RCT at that centre will be given the same analgesia regardless of their treatment allocation (ie, VATS lobectomy or open lobectomy). Local protocols for the provision of analgesia will be defined by the local Principal Investigator (in collaboration with the local research team) prior to the start of recruitment to the RCT. Analgesia administered throughout the participant’s in-hospital stay will be recorded on the trial case report forms (CRFs) and compliance with the predefined and centre-specific analgesia protocols will be monitored.

In order to objectively compare the time from surgery to hospital discharge between VATS lobectomy and open lobectomy, the following discharge suitability criteria have been developed. Study participants will be evaluated against these criteria to ensure that they are medically fit-for-discharge:

Participant has achieved satisfactory mobility.Pain under control with analgesia.Satisfactory serum haemoglobin and electrolytes (ie, does not require intervention).Satisfactory chest X-ray (which will be performed as part of routine clinical care).No complications that require further/additional treatment.

Participants who are considered medically fit-for-discharge may not necessarily be discharged immediately; in some instances, social and other factors may necessitate extended hospitalisation. The time at which participants are considered medically fit-for-discharge and when they are physically discharged from hospital will both be recorded on the trial CRFs.

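### The one planned subgroup factor, type of block, is essentially set by centre, so its interaction test contrasts sets of centres and cannot be attributed to the block

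*Protocol article*

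**What the plan says.** The protocol article, Statistical analysis plan section, names a single subgroup analysis: "One subgroup analysis is planned, comparing pain scores by type of analgesia (paravertebral block vs intercostal block"). On the method it says: "This will be tested by adding an analgesia by treatment interaction term to the model". On centre effects in general it says: "Analyses will be adjusted for centre and for design factors included in the cohort minimisation (eg, the operating surgeon"), and that the "nesting of patients by surgeon and centre, will be accounted for in the primary analysis".

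The Standardisation of postoperative management section sets the rule for analgesia: "each participating centre will prescribe analgesia in accordance with their local protocols". It continues: "All patients recruited to the RCT at that centre will be given the same analgesia regardless of their treatment allocation". The local protocols are defined by each centre's principal investigator "prior to the start of recruitment to the RCT", and "compliance with the predefined and centre-specific analgesia protocols will be monitored".

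On the number of centres, phase 1 has five and phase 2 may add up to five (Trial design). Eight were recruiting at the time of writing (Study status).

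**The concern.** If every trial patient at a centre receives the same analgesia, block type does not vary within a centre except through departures from the local protocol. The interaction is then not a comparison among some 498 patients who differ in block. It compares the average VATS effect in centres that use one block with the average VATS effect in centres that use the other.

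Two consequences follow. First, the centres differ in more than the block. The Randomisation section itself expects variability between surgeons, teams and perioperative processes, and the Trial interventions section permits one to four incisions and other adaptations of technique. Any of these could modify the VATS effect on pain and would be credited to the block. Second, if the treatment effect varies between centres and the model has no term for that, the standard error of the interaction is too small. The trial could then report that the pain benefit of VATS depends on the block when it depends on the hospital.

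The plan treats a comparable non-randomised factor more cautiously. Number of port sites is to be reported as exploratory, without a formal comparison. Block type is formally tested and carries no such label.

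**Working it through.** **1. The plan's own figure.** The article gives no figure for the subgroup. Its overall sample size reproduces, which supports using 498 below. The variance factor for one baseline and five post-surgery measures is (1 + 4 × 0.6)/5 − 0.3² = 0.59. With 0.25 SD, 90% power and two-sided 5% (the alpha is assumed), this gives 199 per arm, 398 in total, and 398/0.8 = 497.5, rounded up to 498.

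**2. What the interaction estimates.** Centre main effects absorb the average level of pain in each centre, and with it any main effect of block. They do not absorb differences between centres in the treatment effect. With block constant within centre, the interaction is the mean of the centre treatment effects under one block minus the mean under the other.

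**3. Error rate when no treatment-by-centre term is fitted.** Inputs: N = 498; C = 8 centres now and 10 at most, taken as equal in size; m = N/C; 1:1 allocation within centre; outcome SD 1. Let τ be the between-centre SD of the treatment effect in outcome SDs. τ is an assumption.

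- Sampling variance of one centre's treatment effect: 4/m. For C = 8, m = 62.25 and 4/m = 0.0643.
- True variance divided by the variance the model assumes: 1 + τ²m/4.
- True type I error: 2(1 − Φ(1.96/√ratio)).

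| τ | 8 centres: ratio | 8 centres: type I error | 10 centres: ratio | 10 centres: type I error |
|---|---|---|---|---|
| 0 | 1.00 | 5.0% | 1.00 | 5.0% |
| 0.1 | 1.16 | 6.8% | 1.12 | 6.5% |
| 0.2 | 1.62 | 12.4% | 1.50 | 10.9% |

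**4. Simulation check.** This used 3,000 replicates, equal centres, centre fixed effects and no true block effect. With 8 centres split 4:4, the rejection rates at τ = 0, 0.1 and 0.2 were 4.8%, 6.8% and 11.7%. Split 2:6, they were 5.2%, 7.4% and 12.9%. A t-test on the eight centre-level treatment effects (6 df) rejected in 4.5% to 6.1% of replicates, with τ taken up to 0.3.

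**5. Price of the corrected test.** For 8 centres split 4:4, the patient-level test with τ = 0 has SE √(16/498) = 0.179. Its smallest interaction detectable with 80% power is (1.96 + 0.84) × 0.179 = 0.50 SD. The centre-level test has SE √((0.0643 + τ²) × 4/8), and the multiplier on 6 df is about 2.45 + 0.91. It detects 0.60, 0.65 and 0.77 SD at τ = 0, 0.1 and 0.2.

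**The case against.** **Detail that belongs in the SAP.** Random-effects structure, degrees of freedom and the classification rule are commonly left to the SAP, which is not shown. That stands for the error rate: an SAP with a random treatment-by-centre slope would repair the p value. It does not dispose of the point, because the article itself fixes both the factor and the test, and its own analgesia rule makes that factor a property of the centre. No choice of standard error removes the confounding.

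**498 independent patients.** A reader might infer that the test ignores centres altogether. The text does not support that. It promises adjustment for centre and surgeon and recognises nesting, though it commits to handling nesting only in the primary analysis. What it leaves unstated is whether the treatment effect may vary by centre.

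**Within-centre variation.** The local protocols are not shown. If one permitted both blocks, or if compliance were imperfect, block would vary within centres to some degree. This is why the factor is called essentially, not strictly, centre-level. Such variation would not be randomised, and the rule as written excludes it.

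**Block actually received.** A reader might also infer that patients will be classified by the block they received, which would bring in decisions made after allocation. Nothing in the article says so.

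**The size of τ.** It is in no document. At τ = 0 the test holds its level, and 0.2 is large beside the 0.25 SD effect on physical function for which the trial is sized. If these centres are taken as fixed, the test validly compares average effects in the two sets. What then remains is the question of attribution.

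**Conclusion.** The point holds. Under the plan's own rule, block type is essentially a centre-level factor with 5 to 10 units, and the planned interaction cannot tell the block from the centre. This follows from the two sections read together and needs no numerical assumption.

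The anti-conservatism is conditional. It requires a model without a treatment-by-centre term and a VATS effect on pain that differs between centres. Under both conditions, an assumed τ of 0.1 to 0.2 SD gives a type I error of 6.8% to 12.4% with 8 centres and 6.5% to 10.9% with 10. It is 5.0% if τ is zero. These figures show what could happen; they do not predict it.

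It would be wrong to infer that the VATS versus open comparison is itself confounded. It is randomised within centre, so each centre's effect is sound, and only the attribution of differences between centres is open. The primary analysis and the sample size are untouched. The consequence is confined to one subgroup analysis of pain scores, but it is the only subgroup analysis planned and it is to be formally tested.

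**What to change.** State in the analysis plan that block type follows the centre's analgesia protocol, and then:

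- Classify participants by the centre's predefined protocol, which already exists before recruitment starts.
- Report how many centres use each block. If all use the same one, the interaction cannot be estimated.
- Fit the interaction with a random treatment-by-centre effect and small-sample degrees of freedom, or test the centre-level treatment effects directly.
- Label the result exploratory and a between-centre comparison.

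This is a change of wording and model specification only, and it implies no change to analgesia practice. The price is a wider interval: about 6 df with 8 centres, and a detectable interaction of 0.60 to 0.77 SD over the assumed range of τ, against a nominal 0.50 SD. That wider interval reflects how little information 8 centres carry on this question.

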### Economic evaluation

The economic evaluation will compare the costs and effects of VATS lobectomy versus open lobectomy, and will follow established guidelines as set out by the National Institute for Health and Care Excellence.^37^ The within-trial cost-effectiveness analysis will be undertaken from an NHS and personal social services perspective, with a 1 year time horizon from the day of surgery. The primary outcome measure for the economic evaluation will be quality-adjusted life-years (QALYs), estimated using the EuroQol EQ-5D-5L, administered at baseline (pre-randomisation) and five time points post-randomisation (see table 1). Resource use data collection will be integrated into the trial CRFs for the index admission for items such as duration of surgery, number of staples used and length of stay; and captured from participants regularly during the 1-year follow-up (see table 1) for events such as hospital readmissions, outpatient attendances and general practitioner (GP) or nurse visits in the community.

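### The economic analysis names no adjustment of QALYs for baseline EQ-5D-5L utility, although it is collected; read literally, the incremental QALY is unbiased but less precise and carries chance baseline imbalance.

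*Protocol article*

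**What the plan says.** All of this is in the Protocol article.

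- **Economic evaluation.** The EQ-5D-5L is "administered at baseline (pre-randomisation) and five time points post-randomisation", so a baseline utility is available. The time horizon is one year.
- **Statistical analysis plan, economic paragraph.** Tariff values are "combined with survival to calculate QALYs gained per participant", missing EQ-5D-5L and resource-use data are multiply imputed, and then: "From the average costs and QALYs gained in each trial group, the incremental cost-effectiveness ratio will be derived". Sensitivity analyses and an acceptability curve follow. The paragraph mentions no regression and no covariate. It also does not call the averages unadjusted.
- **Statistical analysis plan, clinical analyses.** HRQoL scores "will be compared using a mixed regression model, adjusted for baseline measures where appropriate". Primary and secondary outcomes lists the EQ-5D-5L among the HRQoL instruments. A general sentence covers design factors: "Analyses will be adjusted for centre and for design factors included in the cohort minimisation (eg, the operating surgeon").
- **Randomisation.** Cohort minimisation "will be used to ensure balance across groups with respect to the surgeon and the allocation will be stratified by centre". Baseline utility is not balanced by design.

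**The concern.** A participant's utility before surgery predicts the later utilities from which the QALY is built. Only surgeon and centre are balanced, so mean baseline utility will differ between arms by chance, and part of that difference passes into a simple difference in mean QALYs. The article adjusts EQ-5D-5L for baseline when it is analysed as an HRQoL score, but says nothing equivalent when the same responses become QALYs.

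Cost-effectiveness is one of the three specific objectives. The QALY difference is the denominator of the ICER and also drives the acceptability curve. Over one year it may well be small, and a ratio with a small denominator is sensitive to modest shifts. Naming the adjustment in advance also removes the choice between adjusted and unadjusted results once any imbalance has been seen.

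**Working it through.** **1. The plan's own figure.** Sample size calculation gives correlations of 0.3 (pre-post) and 0.6 (between post measures), five post measures, an effect of 0.25 SD and 90% power. I assume two-sided 5%, as the article states no alpha.

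- Variance factor with baseline adjustment: (1 + 4 × 0.6)/5 − 0.3² = 0.68 − 0.09 = 0.59.
- n per arm = 2 × (1.960 + 1.282)² × 0.59 / 0.25² = 198.4, rounded up to 199; total 398. Then 398/0.8 = 497.5, rounded up to 498. Both stated figures reproduce.
- Without the baseline term the factor is 0.68, n per arm is 229 and the total is 458. The design therefore already counts on baseline adjustment for the primary outcome.

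**2. Correlation of baseline utility with the QALY.** The article gives no EQ-5D-5L correlations, so I borrow 0.3 and 0.6 (assumption). I also assume equal SD at each time, the trapezium rule, times measured from randomisation, and no deaths.

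- Times in years: 0, 2/52, 5/52, 0.25, 0.5, 1.
- Trapezium weights: 0.019, 0.048, 0.106, 0.202, 0.375, 0.250 (sum 1).
- Slope of QALY on baseline utility: 0.019 + 0.3 × 0.981 = 0.313.
- QALY variance in units of the utility variance: 0.692 (weights applied to the correlation matrix); square root 0.832.
- Correlation: 0.313/0.832 = 0.377.

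**3. Precision.** Variance removed by adjustment = 0.377² = 0.142, about 14%. Ratio of interval widths, unadjusted to adjusted = 1/√(1 − 0.142) = 1.08.

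**4. Carry-over of a chance imbalance.** With 249 per arm and utility SD 0.20 (assumption; range 0.15 to 0.25):

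- SE of the baseline difference = 0.20 × √(2/249) = 0.0179 (0.0134 to 0.0224).
- Shift in the QALY difference at one SE = 0.313 × 0.0179 = 0.0056, about 0.006 (0.004 to 0.007).
- Shift at 1.96 SE = 0.313 × 0.0351 = 0.011 (0.008 to 0.014).
- SE of the QALY difference: unadjusted 0.20 × 0.832 × √(2/249) = 0.0149; adjusted 0.0149 × √(1 − 0.142) = 0.0138.

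**5. Sensitivity to the pre-post correlation** (SD 0.20, 249 per arm):

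| Pre-post / post-post | Slope | Variance removed | Unadjusted interval wider by | Shift at one SE |
|---|---|---|---|---|
| 0.3 / 0.6 (borrowed) | 0.313 | 14% | 8% | 0.006 |
| 0.5 / 0.6 (assumed) | 0.510 | 37% | 26% | 0.009 |
| 0.5 / 0.7 (assumed) | 0.510 | 34% | 23% | 0.009 |

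**The case against.** The strongest reply is that the sentence only says what an ICER is. Group averages can be regression-adjusted means, and nothing in the economic paragraph excludes covariates. The article condenses a fuller protocol that it points to, and the covariates of a QALY model are often left to such a document or to a health-economic plan. The Economic evaluation section also says that national guidance will be followed, and its content is not shown. This stands against any claim that the article commits to raw averages. A reader might infer that, but the text does not say so.

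Three further replies also stand.

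- A reader might take this to be a bias. It is not: under 1:1 randomisation the difference in unadjusted means is unbiased, and chance baseline imbalance is part of its sampling error, which a correctly computed acceptability curve already reflects. What remains is efficiency, and the shift conditional on the imbalance that actually occurs.
- A reader might infer that the economic analysis ignores centre and surgeon. The general adjustment sentence sits under the same heading and is not limited to clinical outcomes, so that cannot be concluded. It does not name baseline utility, however.
- A slope of 0.5, and so a shift of 0.009 per SE, needs a pre-post correlation of about 0.5. The only such correlation in the article is 0.3, for physical function, which gives about 0.006.

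These replies do not dispose of the point. The article does state how the ICER is formed, and it names baseline adjustment for one use of the EQ-5D-5L but not for the other.

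**Conclusion.** The point holds as a minor improvement. As worded, the economic analysis forms the ICER from group averages without naming an adjustment for a baseline value that the trial collects. Followed literally, it yields a valid but less efficient incremental QALY.

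On the article's own correlations, adjustment removes about 14% of the variance. A one-SE baseline imbalance shifts the increment by about 0.006, against an unadjusted SE of about 0.015, or about 0.38 of that SE (0.0056/0.0149). At a pre-post correlation of 0.5 the variance removed rises to between 34% and 37%.

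These sizes rest on assumptions: the physical-function correlations carried over to EQ-5D-5L, a utility SD of 0.20 (0.15 to 0.25), equal SDs over time and 249 per arm. The article gives no utility SD and no expected QALY gain. A reader might infer that imbalance alone would decide the sign of the result. If the true gain were 0.01 to 0.02 (an assumption), the increment would be imprecise with or without adjustment (SE 0.014 or 0.015), so most of that uncertainty is ordinary sampling error.

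**What to change.** Add to the economic paragraph that incremental QALYs are estimated by regression on treatment with baseline EQ-5D-5L utility as a covariate, together with the centre and design factors that the section already states. The model is fitted within each imputed data set and the results combined. The ICER and the acceptability curve are derived from these adjusted differences. If the full protocol or the health-economic plan already says this, aligning the article's sentence settles the matter.

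The cost is a sentence or two of plan wording and trivial programming. No new data, visits or participants are needed.
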